### Recruitment

All eligible physicians in EMRALD have consented to participate in the study. Although this intervention is multifaceted, it is designed to limit the amount of non-clinical time required by the physicians. The intervention is meant to facilitate physicians to provide the right treatment to the right patient by leveraging available data to use at the point of care. The toolkit can be discussed with physicians at a time that suits them. The pragmatic approach does not require them to participate in ways they do not think will be valuable. As the investigators do not intervene directly upon patients, no patient-level consent process is required. Patients are not directly recruited but are analyzed if they remain part of the participating physician’s roster throughout the trial.

### Embedded process evaluation

We will be able to assess uptake of our toolkit by measuring the number of physicians and the frequency of log-ins to the SAFIRE website. We will also be able to measure the number of clinics that have uploaded our AF tools into their EMRs and the frequency of use and the number of physicians that actually used the tools in their clinical encounters. Finally, we will pursue a qualitative study to assess attitudes and barriers to uptake after the study is completed. Physician participants will be interviewed about the facilitators, barriers, or challenges to the uptake of the toolkit. The qualitative assessment and analysis will be informed by Normalization Process Theory which addresses how new practices are implemented, routinely embedded, and integrated in everyday practice through organizational, team, and individual perspectives [81].

## Discussion

### Strengths and limitations

The most important strength of this protocol is the use of a cluster-randomized trial design to test a clinically important question for large numbers of patients at high risk of stroke. The approach is pragmatic, highly valuing external validity by limiting eligibility criteria and testing a readily scalable suite of interventions tailored to address known barriers to optimal provision of stroke prevention therapy in primary care for patients with AF. We believe that the flexible toolkit approach will engender a sense that the intervention is partially “ground-up” (tailored and customized by participants) rather than completely “top-down” (implemented from the outside in a standardized fashion) leading to more meaningful use of the tools.

We acknowledge several potential limitations. First, the approach to delivering the interventions as a toolkit will make it difficult to determine which particular tools are most effective. While this approach will lead to variation in intervention uptake, it improves external validity, mimicking the real-world setting where providers will only adopt strategies perceived as useful in their context and for their patients. Second, although we have carefully developed tools to address known barriers, it is possible that other interventions may be valuable additions to the current approach or that the tools used will not be optimally tailored for the context. We have attempted to partially address this through a pre-trial phase including a mixed-methods pilot test in which the entire toolkit was tested in a primary care clinic, in keeping with the existing guidance for the development of complex interventions [82]. Third, our primary outcome is a process measure (i.e., appropriate prescribing) rather than a patient-oriented measure (e.g., stroke). We believe this is reasonable given the well-established effectiveness of stroke prevention therapy and believe this compromise is necessary given our desire to complete the analysis in a reasonable time frame. Fourth, our automated assessment of risk factors will be limited to data available in the EMR, and there is variation in the charting habits of family physicians. This may result in challenges for identification of patients with AF; patients with AF that cannot be readily identified will not be included in feedback reports and will not have the AF toolbar activated in their EMR chart. However, variation in charting is expected to be independent of randomization thus limiting risk of misclassification bias. Medications are entered as a structured variable in the chart and should not be affected by idiosyncratic data-entry. We recognize that some primary care clinics may be more likely to refer management of AF to consultants, but again expect that such characteristics would be independent of randomization. Further, if the rate of anticoagulation is far higher than expected, as seen in some studies [17], then we may encounter a ceiling effect. It is also possible that a ceiling effect may be reached due to external factors, such as attention given to this area by pharmaceutical companies. However, we may still find other results of interest in our analysis, including measures related to safety (i.e., appropriately frequent blood work). Finally, it is important to note that participants in EMRALD are a convenience sample of Ontario family physicians using PS Suite® EMR. This may make it difficult to generalize to other providers who use different EMR systems, or to those not using EMR at all. Nevertheless, most of the EMR strategies in the toolkit could be easily adapted to other systems.

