### Participants

Participants will be drawn from the primary care practices associated with the Electronic Medical Record Administrative data Linked Database (EMRALD) in Ontario, Canada. EMRALD is a unique data source that captures complete clinical patient charts already being used by family physicians (thereby avoiding the need for case report forms) [53, 54]. The electronic medical record (EMR) data are extracted and securely stored at the Institute for Clinical Evaluative Sciences (ICES), where it can be linked to population-level administrative health databases. EMRALD provides an opportunity for large-scale initiatives by facilitating centralized, automated chart abstraction, and data analysis using validated database algorithms to assess and provide feedback regarding quality of care. The platform has been used before to facilitate a quality improvement trial [55].

Eligible physicians are those participating in EMRALD, using PS Suite® EMR for at least 2 years, and have 100 or more rostered patients. These eligibility criteria are to ensure that physicians have had sufficient experience with their EMR and have adequate patient data to assess baseline and outcome measures. Eligible patients within EMRALD will have a physician diagnosis of AF recorded in their chart and >18 years of age. No distinction will be made between paroxysmal, persistent, and permanent AF. Analysis will be restricted to adult patients rostered to participating physicians since physicians may not start long-term medications for patients who are not regularly seen at their practice (thus excluding encounters such as “walk-in” patient visits).

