#### Audit and feedback

A Cochrane systematic review found that audit and feedback increases healthcare professionals’ compliance with desired practice by 4.3% (IQR 0.5 to 16%) [57]. We have experienced conducting trials featuring audit and feedback to family physicians, having recently completed a 2-year trial in which participants received data regarding the proportion of patients with diabetes and/or heart disease meeting evidence-based targets [55]. Both aggregate and individual-level data will be provided using data from the physician’s own electronic patient charts through SAFIRE.

Performance will be compared against the median score of the top ten percent of peers, an evidence-based approach to provide an achievable benchmark of care [65]. In addition, drop-down menus allow the user to aggregate the data for all physicians in the practice and compare this to all other intervention practices to facilitate practice-level quality improvement strategies (see Figs. 1a, b for example feedback reports). The design of these reports will match those already delivered to all EMRALD participants (diabetes, heart disease, and hypertension) in addition to AF reports. Both raw numbers and tables are used to help users visualize achievements of quality indicators (and change over time). Based on a qualitative process evaluation of the aforementioned trial [66], the feedback presents both achievements of best-practice quality indicators, and of patients exceeding high-risk thresholds. The patient-level data can be used to sort by patients, any of the quality indicators, or high-risk thresholds. There is also an opportunity for users to exclude individual patients from future reports (see Fig. 1c).

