### Measurement

EMR-based treatment data will be used to identify stroke prevention therapy. Previous work with EMRALD has shown that EMR data regarding active treatments (e.g., warfarin) is comparable to administrative data in terms of drug-capture for patients over age 65 (and far superior for patients under age 65 as drug administrative data in Ontario is limited in patients under 65) [16, 53]. To determine whether the stroke prevention therapy is concordant with guideline recommendations, the EMR data will be used to identify whether patients have relevant comorbidities (i.e., CHADS2 risk factors). The EMRALD team has validated, automated methods for identifying patients with diabetes [55, 74], ischemic heart disease [75], and hypertension [76] using data from both structured fields and free text. Patients identified with these conditions and relevant quality indicators are already included in the online feedback platform.

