### Analysis

Outcomes will be compared at study completion at the patient, provider, and clinic levels. The analysis will be carried out on patient level variables using the generalized estimating equation approach to control for the effects of clustering. We will also adjust for the proportion of patients with guideline-concordant stroke prevention therapy at baseline and the other variables used in the minimization, as recommended by Taves [60]. Analysis will be performed on an intention-to-treat basis, and patient identifiers will be removed before transferring the data securely to analysts so that they will be blind to allocation. We will conduct the analysis as a longitudinal cohort design to permit exploration of patients whose treatments changed over time. As a sensitivity analysis, we will also conduct a repeated cross-sectional analysis to capture patients with newly developed AF during the intervention.

In keeping with similar trials in this literature, we considered a 10% difference in the primary outcome to be clinically important [48]. We assumed that 50% of patients with atrial fibrillation assigned to the usual care arm receive the primary outcome—using a control arm proportion of 50% is a conservative approach as it provides the largest sample size estimation. An EMRALD manual chart review of 7500 randomly selected adult patient charts discovered 192 patients with AF [16]; this 2.6% prevalence is similar to what has been reported in other primary care studies [79]. Based on that pilot data, we estimated that at least 100 patients would be available in each clinic (cluster). Therefore, using a reported intra-cluster correlation = 0.029 for warfarin uptake in patients with AF in primary care clinics [46], setting alpha = 0.05, and after adding 10% inflation for patient loss to follow up, 3276 patients (33 clinics) would be required to have 80% power [80].

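### The primary outcome is read from the chart that the toolkit prompts only intervention clinics to review, so part of any difference between arms could be recording rather than treatment

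*Protocol article*

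**What the plan says.** The Measurement section of the protocol article fixes the data source: "EMR-based treatment data will be used to identify stroke prevention therapy". In support it cites earlier EMRALD work in which chart capture of active drugs was comparable to administrative data over age 65 and far better under 65.

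The toolkit works on the same chart, in intervention clinics only:

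- Audit and feedback: AF reports are built from the physician's own charts, and "The patient-level data can be used to sort by patients, any of the quality indicators, or high-risk thresholds". Notification emails tell clinic delegates how to draw up a list of patients for reassessment. One example given is a CHADS2 score above 1 with no anticoagulation.
- EMR-based clinical decision support: a toolbar prompts physicians to deal with AF at visits made for other reasons. Visit templates include adherence to stroke prevention treatment, and a further tool tracks patients on warfarin.

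The Intervention section says that control clinics do not know of an AF study and keep receiving feedback on other conditions.

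Strengths and limitations expects variation in charting to be independent of randomization and adds: "Medications are entered as a structured variable in the chart and should not be affected by idiosyncratic data-entry". On care given outside the clinic it reasons in the same way: "some primary care clinics may be more likely to refer management of AF to consultants, but again expect that such characteristics would be independent of" the allocation. The Participants section says that EMRALD data are held at ICES, "where it can be linked to population-level administrative health databases". The article describes no check of the primary outcome against those databases.

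**The concern.** The independence argument is sound for characteristics that exist before allocation. A clinic that charts poorly, or that sends its AF patients to consultants, is as likely to fall in one arm as in the other. A structured medication field likewise settles how a drug is entered. Neither point bears on whether a drug started outside the clinic is entered at all, or on whether allocation changes that.

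Take a patient whose consultant started an anticoagulant that the family physician never charted. At baseline this patient counts as untreated in either arm. In an intervention clinic the patient can appear on a list of people without anticoagulation, and one natural response is to add the drug to the chart. The outcome then changes from no to yes with no change in care. A control clinic has no AF prompt to do the same. In the other direction, an adherence review may show that a charted drug was stopped, and removing it lowers the intervention arm's rate.

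Either way, recording error after randomization may differ by arm. Blinded analysts, intention-to-treat analysis, adjustment for baseline and generalized estimating equations leave this untouched, because the error arises at data entry. At stake is whether an observed rise means that more patients are treated, which is what the trial sets out to show.

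**Working it through.** **Inputs from the Analysis section.** Control rate 50%; "we considered a 10% difference in the primary outcome to be clinically important"; "setting alpha = 0.05" (sidedness not stated, two-sided assumed); the sample size "would be required to have 80% power"; 100 patients per clinic; intra-cluster correlation 0.029; 10% inflation for loss; stated total 3276.

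**Inputs not in the documents (assumed).** The share of treated patients whose drug is missing from the chart, and the share of those that each arm charts during follow-up.

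**Step 1: the plan's own figure.** For 50% against 60%, two-sided 0.05 and 80% power without continuity correction, n = 388 per arm (385 with unpooled variance). Design effect = 1 + (100 − 1) × 0.029 = 3.871.

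- Pooled: 2 × 388 × 3.871 × 1.10 = 3304.
- Unpooled: 2 × 385 × 3.871 × 1.10 = 3279.

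Both are within 1% of 3276, so the sample size is not at issue.

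**Step 2: implied precision.** SE = 10 / (1.96 + 0.84) = 3.57 points.

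**Step 3: artefact from newly charted drugs, with no true effect.** Let T be the true percentage treated, m the share of treated patients missing from the chart, and c the *difference between arms* in the share of those who get charted. Artefact = T × m × c.

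| T | m (assumed) | c (assumed) | Artefact | Share of the 10-point target |
|---|---|---|---|---|
| 50% | 2% | 0.5 | 0.5 points | 5% |
| 50% | 5% | 0.5 | 1.25 points | 12.5% |
| 50% | 10% | 0.5 | 2.5 points | 25% |
| 70% | 10% | 0.5 | 3.5 points | 35% |

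**Step 4: chance of a significant result with no true effect.** P(|Z + artefact/SE| > 1.96), nominal 5%, for the rows at T = 50%:

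- 0.5 points: shift 0.5/3.57 = 0.14, chance about 5.2%.
- 1.25 points: shift 0.35, chance about 6.4%.
- 2.5 points: shift 0.70, chance about 10.8%.

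**Step 5: the opposing term.** Let r be the share of untreated patients with an outdated anticoagulant entry, and d the between-arm difference in the share of those entries removed. Net artefact = T × m × c − (100% − T) × r × d. At T = 50%, equal shares and equal gaps (r = m, d = c) cancel exactly. With m = 10%, r = 5% and both gaps 0.5, the net is 2.5 − 1.25 = 1.25 points. The documents give none of m, c, r or d, so the sign is a judgement and not a result.

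**The case against.** Much of the case on the other side stands.

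- **No instruction to correct charts.** A reader might infer that the toolkit tells physicians to update medication lists. It does not. The lists are for reassessment, and users may also exclude a patient from later reports. The example list (CHADS2 above 1) is narrower than the primary denominator (age 65 or over, or CHADS2 of at least 1). Charting an outside drug is a plausible response, but it is inferred.
- **The control arm is not frozen.** A reader might assume that omissions stay in the control arm. Control clinics still get feedback on other conditions and are the intervention arm of the companion kidney disease trial. Both activities, and routine care, can update medication lists. Only the between-arm difference matters, and c is defined that way above.
- **The direction is not assured.** Tools that look for non-adherence can remove outdated entries and lower the intervention arm's rate. The feedback list does single out charts with *no* anticoagulant, which makes a net upward effect the likelier one, but this is not demonstrable.
- **The size may be small.** The Measurement section's comparability statement suggests a modest gap over age 65. Larger inputs give striking figures: 15% missing and a 70% gap yield 5.25 points and about a 31% chance of false significance. Nothing in the documents supports those inputs.
- **The remedy could sit in a fuller protocol or analysis plan.** That is possible, and the absence of such an analysis from a condensed article is not the point. The point is the argument that the article makes.

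The objection does not rescue that argument. The comparability evidence predates the toolkit, comes without a sensitivity figure and was not assessed by arm. The plan also counts AF entry in the cumulative patient profile as a process outcome, so it already treats AF charting as something the toolkit may change.

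**Conclusion.** The point holds in a limited form. The primary outcome and the intervention share one chart, the AF prompt reaches one arm only, and the stated reason for expecting no differential misclassification covers pre-existing habits and entry format but not charting changed by allocation. Part of any observed difference could therefore be recording.

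The size depends on assumptions: about 1.3 to 2.5 points at 50% treated if 5–10% of treated patients are uncharted and the arms differ by half in closing that gap, and less if capture is better. At those values the two-sided false-positive chance is about 6% to 11% in place of 5%. These figures count only the upward term. A net effect in favour of the toolkit is more likely than the reverse, but the documents settle neither sign nor size.

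It does not follow that a positive result would be uninterpretable. Artefacts of this order are an eighth to a quarter of the 10-point target and could not by themselves account for a difference of that size. This is a worthwhile and inexpensive improvement, not a flaw that invalidates the design.

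**What to change.** 1. For patients aged 65 and over, pre-specify a supporting analysis of the primary outcome in which anticoagulant use at baseline and at 12 months comes from linked administrative drug data, with the same model. The article's comparability statement is worded for patients over 65, so check that drug data coverage supports the exact lower age limit.
2. Report chart–claims agreement by arm at both times. A count by arm of newly charted anticoagulants that had already been dispensed before baseline would show the mechanism directly.
3. Interpret the chart-based result in the light of these findings, without making claims support a formal condition for declaring an effect. Such a gate would rest on the older patients alone and leave out younger patients who qualify by CHADS2 score.
4. Reword the limitations text to say that charting habits at baseline are expected to be balanced by randomization, but that the intervention may affect charting during follow-up.

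Cost: one additional linkage, which the article says is possible at ICES, and one additional analysis, with no new data collection from clinics. The limit is that patients under 65 are not covered, because the article describes administrative drug data for them as limited.

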
### Implications

During the trial, the participants of EMRALD (both patients and providers) stand to benefit through improved tools and systems to manage this complicated problem in primary care. Increasing the proportion of patients with adequate stroke prevention therapy will result in improved outcomes for patients and for the health care system. If successful, similar multifaceted strategies may be developed and tested for other high-risk populations in this context.

## Abbreviations

AF: Atrial fibrillation
BP: Blood pressure
CCB: Calcium channel blocker
CCS: Canadian Cardiovascular Society
CI: Confidence interval
CKD: Chronic kidney disease
CME: Continuing medical education
DVT: Deep vein thrombosis
ECG: Electrocardiogram
EMR: Electronic medical record
EMRALD: Electronic Medical Record Administrative data Linked Database
ICES: Institute for Clinical Evaluative Sciences
INR: International normalized ratio
IQR: Interquartile range
LDL: Low-density lipoprotein
NHS: National Health Service (UK)
NOAC: Novel oral anticoagulant
OAC: Oral anticoagulant
PE: Pulmonary embolism
QALY: Quality-adjusted life-years
SAFIRE: System for Audit and Feedback to Improve caRE
TIA: Transient ischemic attack
